## Introduction

### Background

Multiple sclerosis (MS) is one of the world’s most common neurologic disorders leading to severe disability in young adults. More than 2.3 million people live with MS in the world, with higher incidences in Northern Europe and in temperate climates [1]. MS is a chronic condition with high self-management needs [2] that require significant support [3-5] since the majority of self-management occurs at home [6]. MS symptoms range from simple visual disturbances and altered sensation to severe fatigue and cognitive problems with mobility issues [2]. Persons with MS can also go through stretches of periods in which symptoms worsen, called “attacks” or “relapses” [1,2]. Fatigue is the most common and disabling symptom of MS, affecting up to 80% of patients [7-12]. There seems to be some association between MS fatigue and environmental conditions such as the time of the day and weather [13] but it is still unknown how much of an influence these factors have. MS fatigue has a huge impact on quality of life [8,9] and socioeconomic status for persons with MS and is the major reason for early retirement [14]. As a result of MS, persons with MS are typically less active [15] and have reduced levels of physical activity [16-18].

Mobile health (mHealth) is the delivery of health care or health care–related services through the use of portable devices [19]. The use of mHealth software apps has grown in recent years, to the point where commercial app stores hold thousands of health care–related apps [20]. Several digital and remote communication technology apps have been developed for MS clinical monitoring and management, to complement traditional clinical approaches [21]. Wearable devices, including actigraphy, gyroscopes, and body temperature or heart rate monitors, have been used to obtain a more comprehensive assessment of different body functions and to monitor disability in persons with MS [22]. A recent review [21] showed that the use of apps for MS as complements to traditional in-clinic care can improve outcomes and increase access to care, disease information, and support. The use of mHealth could help persons with MS to be more active in their self-management, for example, by tracking adherence to treatment, changes in bladder and bowel habits, and activity and mood.

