## Methods

### Study Design

A mixed-methods, multicenter study will be used to assess the feasibility, acceptability, and usability of More Stamina. The study will take place during the third and fourth quarters of 2020 (Q3-Q4 2020) in 3 locations: Argentina, Spain, and Switzerland.

A longitudinal cohort pilot study will be conducted using a series of well-established standardized tools for user-based evaluations and surveys (see Standardized Tools). Participants’ background information regarding health information, quality of life, and familiarity with mobile technologies will be collected. Potential cultural differences will also be explored through qualitative approaches. System usage logs will quantify patient engagement with the system [50].

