#### Switzerland

Kliniken Valens is a center specializing in neurological rehabilitation services located in Valens, Switzerland. Kliniken Valens employs a multidisciplinary staff, including neurologists, physiotherapists, occupational therapists, speech therapists, and sports therapists. In 2019, a total of 550 persons with MS were admitted for neurological rehabilitation, of which 70% suffered from fatigue and this was the primary focus of their stay.

The Swiss local team will be composed of researchers from Kliniken Valens and the University of Oulu.

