### Data Analysis

#### Quantitative Analysis

Descriptive statistics will be used to summarize the participants’ background and characteristics. Categorical variables will be presented as absolute and relative frequencies. Continuous variables will be presented as mean and standard deviation or median with interquartile range depending on distribution. A *P* value <5% will be considered statistically significant. Statistical analysis will be performed using STATA v15.

Quantitative analysis will be performed on the data collected through the mHealth solution. A linear regression model will be used to assess the association between the degree of adherence to the app, changes in the amount of activity, and changes in the amount of estimated stamina per activity. The outcome variables will be changes between baseline and final activities, changes in estimated stamina per activity for specific activities selected by the researcher team based on frequency and relevance, and changes in fatigue self-perception. Changes will be calculated considering the baseline measurement and final measurement after the 3-month tracking period. A multivariate linear regression model adjusted for age, sex, and eHEALS will be used. The need for inclusion of other potential confounders will be evaluated.

Participants who are above the median usage of the app will be defined as heavy users. The median is less affected by outliers and skewed data and is usually the preferred measure of central tendency when the distribution is not symmetrical. Potential factors associated with the use of the app will be explored with a univariate logistic regression model.

Qualitative analysis will be performed on the data collected through the think-aloud protocol, individual interviews, and focus groups by using thematic analysis to identify emerging themes [62]. Each transcript will be reviewed and coded independently by 2 researchers. The themes will be combined by agreement of the 2 researchers, involving a third researcher in the event of a disagreement. Major themes and subthemes will be developed via an iterative review process. In order to help ensure the integrity of the content analyses, the guidelines recommended by Shenton [63] will be followed, which include collecting and analyzing data in an iterative process to identify themes and generating an audit trail, among others.

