### Limitations

It is possible that the differences between the patient group who participated in the UCD and the target groups of this study are significant enough that there is a preference mismatch. For example, the importance of fatigue management could vary depending on cultural factors or adherence, or interest could even be radically different depending on economic factors. This is expected, and understanding potential differences is part of the aims of the study. Finally, the nature of the study does not allow the assessment of health outcomes due to the lack of randomized exposure and monitoring period. Such explorations will be the subject of future studies.

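### Site, a known three-level design factor, is not assured a place in the adherence regressions, so differences between sites could appear as an adherence association

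*Protocol article*

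**What the plan says.** All of the following is in the protocol article.

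- **Model.** Quantitative Analysis describes one regression approach: "A linear regression model will be used to assess the association between the degree of adherence to the app, changes in the amount of activity". Estimated stamina per activity is handled the same way. The outcomes are change scores and include a patient-reported one: "and changes in fatigue self-perception".
- **Covariates.** The adjustment set is stated: "A multivariate linear regression model adjusted for age, sex, and eHEALS will be used". The next sentence is the only provision for anything else: "The need for inclusion of other potential confounders will be evaluated". It gives no candidates, criterion or timing. Site and country appear nowhere in the section as a covariate, stratum or random effect.
- **Design.** The study runs "in 3 locations: Argentina, Spain, and Switzerland" (Study Design), with at least 20 participants per site and 60 in total (Recruitment and Sample Size).
- **Differences foreseen.** Crosscultural Aspects says that culture shapes how people use technology. It plans to explore the quantitative as well as the qualitative data for cultural and geographical differences, weather among them. It does not connect this to the regression.
- **Use and economics.** Limitations adds that "interest could even be radically different depending on economic factors".
- **Fatigue and weather.** Background says "There seems to be some association between MS fatigue and environmental conditions such as the time of the day and weather", and the same sentence adds that the extent of the influence is not known.

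**The concern.** The article goes as far as naming covariates, and the list omits the one grouping that is built into the design. A single slope fitted across three sites combines two things: the association between adherence and change among participants of the same site, and the association between three site averages. Only the first speaks to the stated objective of estimating the effect of adherence on behavior change and on perceived fatigue management.

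The protocol's own text makes both links of a confounding path plausible. Use may differ between countries, and fatigue may move with weather. The third and fourth quarters also fall in opposite seasons in Buenos Aires and in Europe, so a seasonal drift could enter the change scores differently by site; that step is inference.

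Results are to be judged at a 5% significance level, and the Discussion says the pilot will be a foundation for a larger randomized study. A between-site difference read as an adherence association would be a poor basis for that study.

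**Working it through.** **Inputs from the protocol article**
- Three sites with at least 20 participants each: 3 × 20 = 60, which reproduces the stated total. There is no power calculation to reproduce.
- Covariates: age, sex, eHEALS.
- Significance level 5%; two-sided is assumed, because the article does not say.

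**Assumptions (the documents give no between-site figure)**
- Exactly 20 participants per site, with complete data.
- Within-site SD of 1 for both adherence and the change outcome.
- Site means at −d, 0, +d, with d = dA for adherence and d = dY for change. The extreme sites therefore differ by 2d.
- No association between adherence and change within any site.

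**Step 1: bias of the slope without site.** With three equal groups at −d, 0, +d, the between-site variance of adherence is (2/3)dA² and the between-site covariance is (2/3)dA·dY. Hence

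bias = (2/3)·dA·dY / (1 + (2/3)·dA²).

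- d = 0.25 (extremes 0.5 SD apart): 0.0417 / 1.0417 = 0.04
- d = 0.50 (1 SD apart): 0.1667 / 1.1667 = 0.143
- d = 0.75 (1.5 SD apart): 0.375 / 1.375 = 0.273

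**Step 2: false rejection rate without site.** Five coefficients are estimated (intercept, adherence, age, sex, eHEALS), so residual df = 60 − 5 = 55 and the critical t is 2.004. The residual variance is 1 + (2/3)dY² − bias²·(1 + (2/3)dA²), and SE ≈ √[residual variance / (60·(1 + (2/3)dA²))].

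| Gap between extreme sites | Bias | SE | Bias/SE | Rejection (noncentral t) |
|---|---|---|---|---|
| 0.5 SD | 0.040 | 0.129 | 0.31 | 6% |
| 1 SD | 0.143 | 0.128 | 1.12 | 20% |
| 1.5 SD | 0.273 | 0.124 | 2.20 | 58% |

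Simulation of the same model, with 3,000 runs per setting, gave 6%, 19% and 57%.

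**Step 3: the same simulations with two site indicators added.** The mean adherence coefficient was within 0.01 of zero and the rejection rate was 4–6% in every setting.

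**Step 4: when there is no problem.** If sites differ in adherence only, or in change only, the formula gives zero bias, and the simulated rejection rate without site was 4–6%. The ordering also matters. Adherence means of −d, 0, +d combined with change means of e, −2e, e have covariance proportional to (−d)(e) + 0 + (d)(e) = 0, so no bias arises. If the two orders are reversed, the bias is negative.

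**Step 5: cost of including site.** Residual df falls from 60 − 5 = 55 to 60 − 7 = 53, and the critical t moves from 2.004 to 2.006. With no site differences and a standardized slope of 0.38 (an illustrative value), simulated power falls from 78% to 76%.

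**The case against.** **Site is not excluded.** The sentence on other confounders leaves it open, and Crosscultural Aspects plans to examine geographical differences in the quantitative data. This stands. A reader might infer that the protocol commits to a pooled model without site; it does not. Pooling is implied by the single model described, and the fault is only that a factor known from the design is left to an unspecified evaluation. Nor does the article's brevity dispose of the point, since it does list covariates.

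**The protocol does not say that site affects adherence and fatigue.** This also stands. The Limitations passage compares the group from the design phase with this study's target groups, not the three sites with one another. The weather association is tentative and of unknown size. The Swiss description, of patients "admitted for neurological rehabilitation, of which 70% suffered from fatigue and this was the primary focus of their stay", concerns one clinic's 2019 admissions and not the study sample. Background puts fatigue at up to 80% of patients generally, so the 70% does not mark that site out.

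**Levels are not changes.** The outcomes are within-person changes, and a site difference in fatigue level alone need not bias them. This is correct: site must relate to change and to adherence, and no passage says that it does. The fatigue and weather text is also silent on the two activity-based outcomes.

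**Selection of covariates after seeing outcomes is not described.** A reader might infer it from the open clause, but the article gives neither timing nor criterion. What can fairly be said is that nothing prevents it.

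**The consequences are limited.** This is a feasibility pilot, and Limitations disclaims assessment of health outcomes. That lowers the stakes. The objectives nevertheless speak of estimating effects of adherence, and a significance level is set.

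**Conclusion.** The point holds in a limited form. The adherence regressions are adjusted for age, sex and eHEALS only, and site has no assured place in them. If site is related to both adherence and change, the slope can show a spurious association of either sign.

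How large this would be cannot be found from the documents. At a 0.5 SD gap the harm is negligible, at 1 SD the error rate is about four times nominal, and at 1.5 SD more than half of tests would reject. These figures assume that the sites are ordered identically on both variables, which is an unfavorable pattern; other orderings can give less bias or none. They show what could happen, not what is expected.

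The documents do not support the stronger statement that site is a confounder on the protocol's own terms. The case for change rests on the low cost of including a known design factor and the absence of any stated reason to leave it out.

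**What to change.** In Quantitative Analysis:

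1. Name site as a fixed three-level factor, alongside age, sex and eHEALS, in the adjusted linear regressions of change on adherence.
2. State, before outcome data are examined, which other confounders will be considered.
3. Report adherence by site descriptively and call the contrasts site differences. With one site per country, culture, care setting and season cannot be separated.

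The cost is a change of wording, two residual degrees of freedom (55 to 53) and about two points of power in the illustration above. Adding the baseline value and EDSS is optional, would take two further degrees of freedom (53 to 51), and is not needed for this point. The exploratory univariate logistic model for factors associated with use can stay as it is.

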### Objectives

The overall study aims are to explore the feasibility, acceptability, and usability of More Stamina, a mobile app for fatigue self-management for persons with MS.

The specific objectives are to estimate adherence to the use of More Stamina; estimate the effect of More Stamina adherence on behavior change, measured through changes in the amount of activities and amount of estimated energy per activity; estimate the effect of adherence to the use of More Stamina on the perception of fatigue management; validate the value proposition of More Stamina; identify More Stamina user activity patterns of persons with MS; and identify factors associated with the use of More Stamina.

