### Recruitment and Sample Size

Persons with MS will be recruited from patient databases at HIBA, VNH, and Kliniken Valens and invited to participate in the study. Inclusion criteria will require each participant to be >18 years old, have received a confirmed MS diagnosis according to McDonalds criteria [51] at least 1 year prior to the study, have none to moderate physical disability (Expanded Disability Status Scale [EDSS] <6.5) at the time of recruitment, have no major cognitive or haptile impairment influencing the ability to use the app, be fluent in one of the languages in which More Stamina is available, and be the owner or user of a compatible smartphone device with internet access.

Exclusion criteria include refusal to participate, cognitive or physical impairment that prevents the use of mobile phones, and inability to attend the follow-up encounters.

This study seeks to enroll at least 20 patients that meet the criteria from each site for the longitudinal cohort study (total n=60). The sample size is an adequate number because of the methods used that provide extensive, detailed data [52].

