#### User Behavior

Within More Stamina, Stamina Credits are a numeric continuous variable that ranges from 0 to 100 to represent the estimated effort of an activity. This variable is used to gauge how effective the user is in predicting the effort of each individual activity.

User activity patterns over time will be aggregated per week and described. Adherence will be estimated in each follow-up meeting. Adherence with app use will be estimated using the frequency of weekly use throughout the tracking period.

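### Splitting app use at the sample median for the factors-of-use analysis loses power and yields a purely relative 'heavy user' label; analyse use ungrouped

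*Protocol article*

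**What the plan says.** The relevant text is in the protocol article, Methods, under Quantitative Analysis. It defines the group: "Participants who are above the median usage of the app will be defined as heavy users". Its reason begins "The median is less affected by outliers and skewed data" and goes on to call the median the usual measure of centre for asymmetric distributions. The next statement is "Potential factors associated with the use of the app will be explored with a univariate logistic regression model". This serves the last of the specific objectives, to "identify factors associated with the use of More Stamina".

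Two other places matter:
- User Behavior says how use is measured: "Adherence with app use will be estimated using the frequency of weekly use throughout the tracking period".
- Quantitative Analysis also uses adherence without grouping: "A linear regression model will be used to assess the association between the degree of adherence to the app", with changes in activity and in estimated stamina. A multivariable version of that model adjusts for age, sex and eHEALS.

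No absolute threshold for heavy use is given anywhere, and no distribution of use is stated or assumed.

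**The concern.** The split has three weaknesses.

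1. **The reason does not support the step.** Robustness to skew is a reason to report a median. It is no reason to replace a graded measure by two groups. Skew can be handled by ordinal, rank-based or binomial-type methods without discarding the ordering within each half.
2. **Power.** With about 60 participants, a real association between use and, say, eHealth literacy is more likely to be missed after the split than before it.
3. **Meaning.** The cut is set by the sample. A cohort that hardly opens the app and one that uses it almost daily both produce heavy users, and an odds ratio for being above the median refers to a different level of use in each.

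What is at stake is the reading of one exploratory objective. As a secondary matter, factors are examined one at a time, so their effects cannot be separated if they are correlated.

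**Working it through.** **Inputs from the document.** At least 20 participants at each of 3 sites, 3 × 20 = 60 (Recruitment and Sample Size). Significance at P below 5% (Quantitative Analysis); sidedness is not stated, so two-sided is assumed. Use is a weekly frequency (User Behavior) from daily measurements (Study Flow). There is no power statement to reproduce.

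**Assumed effect.** By Fisher's z, the correlation that 60 participants detect with 80% power is tanh[(1.960 + 0.842)/√(60 − 3)] = tanh(0.371) = 0.355. A latent correlation of 0.354 between factor and use therefore represents an effect that a good ungrouped analysis should usually find.

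**Simulated power, n = 60, latent correlation 0.354, 3000 replicates, Wald test in the logistic model:**

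| Assumed distribution of use | Linear, raw scale | Rank-based (Spearman) | Median split, logistic |
|---|---|---|---|
| Normal | 0.80 | 0.76 | 0.58 |
| Log-normal (log-SD 1) | 0.64 | 0.76 | 0.57 |
| Days used out of 60 | 0.76 | 0.75 | 0.58 |
| Rounded days per week, high use | 0.75 | 0.72 | 0.55 |

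A second simulation of the same four types of distribution gave 59–63% for the split and 71–77% for the rank-based test. The choice of test accounts for the higher split figures: a likelihood-ratio test in the logistic model gives values in that range, a few points above the Wald test. The more favourable 59–63% is used for the conclusion. From the ends of those ranges, the loss lies between 71 − 63 = 8 and 77 − 59 = 18 percentage points.

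**Asymptotic efficiency.** Near the null, relative to linear regression on the same scale, the split retains 4·f(m)²·σ² of the information, where f(m) is the density at the median and σ² the variance.
- Normal: 2/π = 0.637, a loss of 36%. Then 60 × 0.637 = 38.2, and 60 × π/2 = 94.2 would be needed to compensate.
- Uniform: 4 × 1/12 = 0.33, a loss of 67%.
- Logistic: 4 × (1/16) × π²/3 = 0.82, a loss of 18%.
- Exponential: 4 × 0.25 × 1 = 1.00, no loss.
- Log-normal, log-SD 0.25, 0.5, 0.75: 0.70, 0.93, 1.50.

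Against raw-scale linear regression the loss therefore depends on the distribution and can reverse under strong skew. If use is normal after a log transform, the loss against the log-scale analysis is again 36%.

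**Share labelled heavy.** The rule is strictly above the median, so the share cannot exceed half. Without ties it is 50%. For days out of 60 the simulated mean was 49% (minimum 40%). For coarse days per week with ties at the ceiling the mean was 40% and the minimum 0%, which occurs when the median equals the maximum.

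**Movement of the cut.** In single illustrative cohorts of 60:

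| Mean use (days per week) | Median cut (days out of 60) | Share heavy |
|---|---|---|
| 0.5 | 1 | 43% |
| 3 | 25.5 | 50% |
| 6 | 53 | 48% |

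In the first cohort, 2 days of use in 60 would count as heavy.

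**The case against.** The strongest reply is that little depends on this analysis. It serves the last-listed objective, is described as exploratory, and sits in a pilot that makes no power claim. Low use would not stay hidden: User Behavior has weekly use described and adherence estimated from its frequency, and the linear models take adherence ungrouped. The link between the logistic model and the heavy-user label is also an inference, though the only one the text allows. All of this stands, and it limits the weight of the point. It does not supply a reason for the split.

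Some stronger readings are tempting but not supported:
- A reader might infer that the split discards over a third of the information, so that 60 participants act like 38. That needs normal use, possibly after transformation. The document gives no distribution and itself anticipates skew, and against raw-scale linear regression the gap narrows or vanishes under strong skew.
- A reader might infer that half the cohort is always labelled heavy. With a bounded weekly frequency, ties can bring the share well below half.
- A reader might blame the univariate form for the loss of information. The split causes that loss; the univariate form raises a separate question of adjustment. The candidate factors are not listed, so their correlation is conjecture.
- A reader might suppose that these odds ratios will be carried into the later randomised study. The Discussion says only that the pilot should clarify issues and challenges as a foundation for it.

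**Conclusion.** The point holds as a modest one. The stated rationale does not justify dichotomising a measure that is already available ungrouped. Assuming n = 60, two-sided 5% and a latent correlation of 0.354, power falls from 71–77% with a rank-based analysis to about 59–63% with the split, under all four usage distributions tried. The size of the loss depends on a distribution that the document does not give; the efficiency of 2/π = 0.64 is one case within a range. That at most half the cohort is heavy, whatever the absolute use, follows from the definition alone and needs no distributional assumption. The estimates of adherence, the linear models and the usability results are not affected.

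**What to change.** - Analyse use ungrouped with a method that respects its bounds and skew: a proportional-odds or other ordinal or rank-based model for weekly frequency, or a binomial-type model for days used out of days observed, allowing for overdispersion. An unbounded count model such as the negative binomial suits this bounded measure poorly when use is high.
- Name the outcome of the model, and report estimates with confidence intervals.
- Keep above-median use as a descriptive label only, and report the value of the cut beside it.
- As a secondary change, add to the one-at-a-time estimates a model with a small prespecified set of factors already collected, such as the age, sex and eHEALS used in the linear models.
- Fix the window over which use is counted. Study Flow gives 2 months of monitoring and Quantitative Analysis a 3-month tracking period; these must be reconciled before days observed can be defined.

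The cost is a change of analysis wording, slightly more analysis work and an effect measure less simple than an odds ratio for two groups. No new data, visits or participants are needed.
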